# Effects of foot intensive rehabilitation (FIRE) on clinical outcomes for patients with chronic ankle instability: a randomized controlled trial protocol

**DOI:** 10.1186/s13102-023-00667-7

**Published:** 2023-04-09

**Keywords:** Ankle injury, Muscle, Plantar sensation, Therapeutics, Secondary prevention

## Abstract

**Background:**

Lateral ankle sprains account for a large proportion of musculoskeletal injuries among civilians and military service members, with up to 40% of patients developing chronic ankle instability (CAI). Although foot function is compromised in patients with CAI, these impairments are not routinely addressed by current standard of care (SOC) rehabilitation protocols, potentially limiting their effectiveness. The purpose of this randomized controlled trial is to determine if a Foot Intensive REhabilitation (FIRE) protocol is more effective compared to SOC rehabilitation for patients with CAI.

**Methods:**

This study will use a three-site, single-blind, randomized controlled trial design with data collected over four data collection points (baseline and post-intervention with 6-, 12-, and 24-month follow-ups) to assess variables related to recurrent injury, sensorimotor function, and self-reported function. A total of 150 CAI patients (50 per site) will be randomly assigned to one of two rehabilitation groups (FIRE or SOC). Rehabilitation will consist of a 6-week intervention composed of supervised and home exercises. Patients assigned to SOC will complete exercises focused on ankle strengthening, balance training, and range of motion, while patients assigned to FIRE will complete a modified SOC program along with additional exercises focused on intrinsic foot muscle activation, dynamic foot stability, and plantar cutaneous stimulation.

**Discussion:**

The overall goal of this trial is to compare the effectiveness of a FIRE program versus a SOC program on near- and long-term functional outcomes in patients with CAI. We hypothesize the FIRE program will reduce the occurrence of future ankle sprains and ankle giving way episodes while creating clinically relevant improvements in sensorimotor function and self-reported disability beyond the SOC program alone. This study will also provide longitudinal outcome findings for both FIRE and SOC for up to two years. Enhancing the current SOC for CAI will improve the ability of rehabilitation to reduce subsequent ankle injuries, diminish CAI-related impairments, and improve patient-oriented measures of health, which are critical for the immediate and long-term health of civilians and service members with this condition.

*Trial Registration* Clinicaltrials.gov Registry: NCT #NCT04493645 (7/29/20).

**Supplementary Information:**

The online version contains supplementary material available at 10.1186/s13102-023-00667-7.

## Background

In the US civilian population, lateral ankle sprains occur at a rate of 2 per 1000 person-years, which creates lifetime costs ranging from $9,196 to $11,925 per patient [1, 2]. The burden of ankle sprains is even higher in military personnel, with the incidence found to be up to 13 per 1000 person-years in officers and 29 per 1000 person-years in enlisted service members [3], representing 13% of all musculoskeletal injuries incurred by this population [4, 5]. The associated morbidity of lateral ankle sprains is compounded by the 40% of patients who subsequently develop chronic ankle instability (CAI), which is characterized by ongoing pain, ankle joint instability, repetitive injury recurrence, and persistent functional disability [6]. The symptoms and recurrence experienced by individuals with CAI are a consequence of persistent mechanical and neurophysiological impairments [7, 8], which contribute to early onset post-traumatic ankle joint osteoarthritis [9–12], deteriorations in physical activity, and declines in health-related quality of life that persist throughout the lifespan [13–17]. For individuals with CAI who seek medical care, management usually consists of palliative medication, basic rehabilitation exercises, and activity modification [18, 19]. Given the relative recalcitrance of CAI and the impact of persistent symptoms on joint and general health, it is clear that the standard of care (SOC) is inadequate for many patients [20].

Impaired joint motion, sensorimotor function, and balance are thought to contribute to repetitive joint trauma and short- and long-term self-reported disability in individuals with CAI [7, 8]. As a result, balance training, ankle strengthening, and range of motion exercises have become the core tenets of the standard of care for CAI rehabilitation [19, 21, 22]. While deficits in balance, ankle strength, and range of motion are regularly targeted during rehabilitation for patients with CAI, recent studies have indicated that many patients do not achieve clinically relevant improvements in sensorimotor function or health-related quality of life [23, 24]. Based on these findings and the complex neurophysiological nature of CAI, the current SOC may not address the full continuum of impairment and disability for patients with CAI. Therefore, there is a critical need to develop rehabilitation strategies that target unheeded impairments to improve the immediate and long-term outcomes for patients.

The foot provides critical somatosensory input, local stability to maintain a base of support, and is an integral component for force generation and attenuation during high energy activities. Preliminary research has identified intrinsic foot muscle (IFM) atrophy and activation deficits [25]; decreased hallux and lesser toe strength [26], and diminished plantar cutaneous sensitivity [27] in patients with CAI. These findings suggest that local foot stability and sensory input, critical for maintaining postural control, may be compromised. Despite these findings, somatosensory, motor, and mobility deficits in the foot are not routinely addressed in rehabilitation.

Interventions targeting IFM activation and plantar cutaneous sensation have demonstrated potential for improving sensorimotor function and health-related quality of life in patients with CAI [28–31]. Clinically relevant levels of activation have been achieved within IFMs using a series of foot core exercises, which focus on foot doming and isolated toe movements [32]. These exercises can improve dynamic balance, somatosensory and proprioceptive acuity, and reduce the severity of perceived instability in patients with CAI following small scale randomized controlled trials [29, 30]. Additionally, plantar massage interventions targeting somatosensory input from the foot have demonstrated the ability to improve single limb balance and health-related quality of life in CAI patients [28]. However, IFM exercises and plantar massage have only been studied in CAI patients in isolation and longitudinal outcomes following intervention have been limited. The additive effect of foot-related interventions to other evidenced-based interventions frequently employed in the SOC has not been examined [19]. Combining foot-related interventions with balance training, strengthening, and range of motion exercises may lead to greater improvements in sensorimotor function, health-related quality of life, and recurrent ankle injury rates.

Addressing sensorimotor function by correcting foot impairments and enhancing local foot stability could provide key additives to the current SOC rehabilitation protocol that could help to achieve more successful clinical outcomes in patients with CAI. Therefore, the overall objective of this randomized controlled trial is to examine the effects of a 6-week Foot Intensive REhabilitation intervention (FIRE) on ankle sprain re-injury and giving way rates, sensorimotor function, and self-reported disability in patients with CAI. Our central hypothesis is that by addressing the sensorimotor deficits at the foot we will reduce the occurrence of future ankle sprains and ankle giving way episodes, create clinically relevant improvements in sensorimotor function, and reduce self-reported disability beyond the SOC intervention alone*.* This study will be guided by the following specific aims:Specific Aim 1 Determine if a 6-week FIRE intervention decreases recurrent ankle sprain rates, frequency of ankle giving way episodes, and perceived symptom severity relative to a SOC intervention in patients with CAI.Specific Aim 2 Determine if FIRE improves sensorimotor function (static and dynamic balance, IFM activation, ankle/toe strength, somatosensation) relative to SOC in patients with CAI.Specific Aim 3: Determine if FIRE improves self-reported disability (foot and ankle function, sport-related disablement, injury-related fear) relative to the SOC in patients with CAI.

## Methods

### Summary and design

This clinical trial will employ a multisite, single-blinded parallel group randomized controlled trial design where patients will enroll at one of three sites: the University of Kentucky, the University of Virginia, or Naval Hospital Camp Pendleton (in partnership with the study teams at Naval Health Research Center). The framework of this design is to assess the superiority of the FIRE intervention in conjunction with SOC over SOC alone. This clinical trial was registered in the United States National Library of Medicine through ClinicalTrials.gov (NCT04493645). Table 1 details the key information pertaining to the registered trial. Ethical approval was granted by the University of Kentucky Institutional Review Board (#58,500), with reliance agreements and ethical approvals granted from the University of Virginia and the Naval Health Research Center in compliance with the single IRB protocol. This protocol has also been reviewed and approved by the Human Research Protection Offices of the U.S. Army Medical Research and Development Command Office of Research Protections and the US Marine Corps. Informed consent will be obtained in writing from all patients prior to enrollment. This work was supported by the Congressionally Directed Medical Research Programs ([name]; [contact]; [contact]), grant W81XWH-20-2-0035. Outside of the human research protection review, the funding sponsor does not have direct role in directing study design; collection, management, analysis, and interpretation of data; writing of the report; or the decision to submit the report for publication. The CONSORT Statement for Randomized Trials of Nonpharmacologic Treatments [33], the template for intervention description and replication (TIDieR) [34], and Standard Protocol Items: Recommendations for Interventional Trials (SPIRIT) 2013 [35] were used to guide reporting.

**Table 1 Tab1:** Trial registration data

Data category	Information
Primary registry and trial identifying number	ClinicalTrials.gov NCT04493645
Date of registration in primary registry	30 July 2020
Secondary identifying numbers	58,500; CDMRP-OR190060 (Other Grant/Funding Number: Department of Defense)
Source(s) of monetary or material support	Congressionally Directed Medical Research Programs
Primary sponsor	Congressionally Directed Medical Research Programs
Secondary sponsor(s)	NA
Contact for public queries	[name], MS, [name], [contact]; [name], ATC, [name], [contact]
Contact for scientific queries	[name], ATC, Sports Medicine Research Institute, University of Kentucky
Public title	Ankle Instability Using Foot Intensive Rehabilitation
Scientific title	Optimizing Clinical Outcomes for Patients with Chronic Ankle Instability Using Foot Intensive Rehabilitation
Countries of recruitment	United States
Health condition(s) or problem(s) studied	Ankle Injuries; Ankle Sprains
Intervention(s)	Active comparator: Foot Intensive Rehabilitation (FIRE) and Standard of Care Rehabilitation (SOC). 6 weeks of FIRE will be given along with elements of SOC. Each patient will be expected to complete 2 supervised sessions and 3 unsupervised at home sessions per week
	Control comparator: Standard of Care Rehabilitation. 6 weeks of SOC rehabilitation will be given designed to restore ankle joint range of motion, strength, postural control, and functional movement. Each patient will be expected to complete 2 supervised sessions and 3 unsupervised at home sessions per week
Key inclusion and exclusion criteria	Ages eligible for study: 18 to 44 years; Sexes eligible for study: both; Accepts healthy volunteers: no
	Inclusion criteria: Aged 18–44; Previous history of at least 1 ankle sprain and at least 2 episodes of "giving way" in the past 3 months; Patients must answer "yes" to at least 5 questions on the Ankle Instability Instrument; Score of 11 or higher on the Identification of Functional Ankle Instability (IdFAI); Confirmed clinical presentation of CAI by a PT, AT, or MD
	Exclusion criteria: Sustained an ankle sprain in the previous four weeks or lower extremity neuromusculoskeletal injury other than to the ankle in the last 12 months; History of surgery to the lower extremity; Sustained a lower extremity fracture; History of neurological disease, vestibular or visual disturbance or any other pathology that would impair their sensorimotor performance; Current participation in a formal ankle joint rehabilitation program; Sustained a concussion in the last 12 months; Exhibit clinical examination characteristics of foot and ankle function which are consistent with conditions other than CAI (i.e. fracture, deformity)
Study type	Allocation: Randomized; Intervention Model: Parallel Assignment; Intervention Model Description:The investigators will compare clinical and innovative outcome measures collected at five time points between cohorts of patients with CAI that receive a standard of care (SOC) rehabilitation program compared to an innovative foot intensive rehabilitation (FIRE) program to determine if FIRE can further reduce the rate of re-injury, improve sensorimotor function, and reduce self-reported disability during the 24 months following the intervention.; Masking: Single (Outcomes Assessor); Masking Description: The investigators collecting the outcomes will be blinded to group allocation. Separate investigators will be used for intervention delivery and outcomes assessment. Primary Purpose: Treatment
Date of first enrolment	October 2021
Target sample size	150
Recruitment status	Recruiting
Primary outcome(s)	Number of recurrent ankle sprains [Time Frame: 24 months]: The ability of FIRE to attenuate the occurrence of ankle sprains compared to SOC rehabilitation will be determined through self-report. An ankle sprain will be operationally defined as an incident in which the rearfoot was inverted or supinated and resulted in a combination of swelling, pain, and time lost or modification of normal function for at least one day Frequency of episodes of the ankle giving way [Time Frame: 24 months]: The ability of FIRE to attenuate the number of episodes of the ankle giving way compared to SOC rehabilitation will be determined through self-reported occurrences per week in the past month. Episodes of giving way will be operationally defined for the patient as an incident in which the rearfoot suddenly rolled, felt weak, or lost stability; however, the individual did not sustain an ankle sprain and was able to continue with normal function Severity of chronic ankle instability related symptoms [Time Frame: 24 months]: The ability of FIRE to attenuate the severity of related symptoms compared to SOC rehabilitation will be determined through the Cumberland Ankle Instability Tool. The Cumberland Ankle Instability Tool is a 9-item instrument used to identify self-reported impairments associated with CAI. This instrument is scored on a 0–30 scale, where lower scores represent greater severity of CAI related symptoms
Key secondary outcomes	Postural Control [Time Frame: 12 months]: The ability of FIRE to improve static and dynamic postural control compared to SOC rehabilitation will be determined. Multiple measurements will be made including: Single-limb stance on each limb with eyes open and eyes closed with use of a force plate for center of pressure measurements, Star Excursion Balance Test, forward jump single limb landing stabilization task. All measurements will be monitored while the patient wears an inertial sensor placed on the lumbar spine Ankle/Toe Strength [Time Frame: 12 months]: The ability of FIRE to improve strength compared to SOC rehabilitation will be determined. Strength of the muscles surrounding the ankle and the toes will be assessed through a series of assessments with a digital handheld dynamometer Intrinsic Foot Muscle Activation [Time Frame: 12 months]: The ability of FIRE to improve foot muscle activation compared to SOC rehabilitation will be determined. Abductor hallucis, flexor digitorum brevis, quadratus plantae, and flexor hallucis brevis functional activity ratios will be captured using diagnostic ultrasound with a 12–4 MHz linear array transducer probe and measured using Image J software Plantar Cutaneous Sensation [Time Frame: 12 months]: The ability of FIRE to improve plantar cutaneous sensation compared to SOC rehabilitation will be determined. Plantar cutaneous sensation will be tested using a 20-piece Semmes–Weinstein Monofilament kit which has monofilaments ranging from to 0.008 g of force (1.65 level) to 300 g of force (6.65 level). Light touch detection thresholds will be assessed on the plantar surface at the 1st metatarsal head

### Patients

One hundred and fifty men and women (*n* = 50 at each site) will be recruited from the campuses and surrounding communities associated with the University of Kentucky, University of Virginia, and Naval Hospital Camp Pendleton through posted flyers, social media postings, and word of mouth at local sports medicine clinics. The university-based sites are sports medicine laboratories located in suburban academic settings in Lexington, KY and Charlottesville, VA. The military site is an outpatient sports medicine clinic located at Marine Corps Base Camp Pendleton that provides specialized primary and referred care to military beneficiaries consisting primarily of US Marines and Navy Sailors. At all three sites, potential patients will be pre-screened by telephone or in-person by a local member of the research team using a checklist containing components of the inclusion and exclusion criteria. Patients who appear eligible based on prescreening and have continued interest in participating in the study will be scheduled to meet with a member of the research team who trained to perform the enrollment and informed consent process.

The procedures for assessing eligibility were derived and aligned with the guidelines for selecting CAI patients from the International Ankle Consortium [36]. To be included, patients must be a male or female adult, aged 18–44 years with a history of ≥ 1 ankle sprain. Patients must also report ≥ 2 episodes of “giving way” in the past 3 months. An ankle sprain will be defined as an injury in which the rearfoot was inverted or supinated and resulted in a combination of swelling, pain, and time lost or modification of normal function for at least one day [37]. Episodes of giving way will be described as an incident in which the rearfoot suddenly rolled, felt weak, or lost stability; however, the individual did not sustain an ankle sprain and will have been able to continue with normal function after the incident [37]. In addition, patients must answer “yes” to ≥ 5 questions on the Ankle Instability Instrument and ≥ 11 on the Identification of Functional Ankle Instability [38]. In cases of bilateral CAI, the limb with the higher Identification of Functional Ankle Instability score will be identified as the involved limb for intervention.

Patients will be excluded if their involved limb sustained an ankle sprain within four weeks, lower extremity injury within twelve months, history of lower extremity surgery or fracture, or concussion within 12 months, conditions other than ankle sprain that affect balance or cutaneous sensation, or they are receiving ankle rehabilitation at the time of screening. The investigator at each site completing the patient enrollment will also perform a basic clinical examination of the ankle that will include tests of ankle ligamentous laxity and joint restriction, foot and ankle fracture, point tenderness, and ankle–foot deformity. The investigators performing these procedures will have professional training in orthopaedic evaluation and will determine if the clinical presentation of the patient is consistent with CAI. If a patient exhibits signs of ankle–foot conditions that are not consistent with CAI, they will be excluded from participation.

### Procedures

The SPIRIT flow diagram detailing study procedures can be found in Fig. 1. Once a patient provides written consent and is deemed eligible to be enrolled in the study, they will be assigned a patient identification number and randomized to either the FIRE or SOC group. A randomization schedule will be prepared by an investigator ([name]) not involved in data collection or intervention delivery using statistical software (SAS v9.4 PROC PLAN). Within each site, 50 patients will be randomly assigned to one of two groups (FIRE or SOC group). To ensure balance in groups over time, randomization will be completed in sequential sets of 10 subjects (5 FIRE and 5 SOC) within each site. Randomization plans include an additional 30 subjects to account for anticipated attrition during the study. Once completed, the randomization plan will be provided to the study coordinator at each site. The investigators will be blinded to group allocation by concealing assignments in sealed opaque envelopes. The treating rehabilitation specialist will retrieve the group assignment from the envelope following collection of baseline data.

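### The completed randomisation list goes to each site's study coordinator, so upcoming allocations can be known at the site before a patient is enrolled

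*Protocol article*

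**What the plan says.** All the allocation steps are in the Procedures section of the protocol article. An investigator outside data collection and intervention delivery prepares the schedule in SAS. Allocation is blocked by site: "randomization will be completed in sequential sets of 10 subjects (5 FIRE and 5 SOC) within each site". The list is longer than the recruitment target: "Randomization plans include an additional 30 subjects to account for anticipated attrition during the study". The next step, taken once the plan is complete, is the one at issue: "the randomization plan will be provided to the study coordinator at each site". Concealment is then described: "The investigators will be blinded to group allocation by concealing assignments in sealed opaque envelopes". Finally, "The treating rehabilitation specialist will retrieve the group assignment from the envelope following collection of baseline data".

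Other sections say who does what at a site. Under Patients, a local member of the research team prescreens, and a trained team member handles enrolment and consent. The enrolling investigator at each site also examines the ankle and judges whether the presentation fits chronic ankle instability. Under Interventions, the treating clinicians book the rehabilitation sessions. Table 1 gives masking as outcome assessor only. The coordinator is mentioned once, as recipient of the plan, and is given no other duty.

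**The concern.** An independent preparer protects concealment only while the sequence stays away from the people who recruit. Sending the whole plan to a role based at each site gives up much of that protection. The envelopes still work for anyone without the list, but they cannot conceal anything from the person who has it.

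What is at stake is selection bias. Consent and eligibility come first, then baseline testing, then the envelope. Throughout that sequence a list-holder could know which arm comes next. There is room to act on such knowledge: prescreening is local, visits have to be scheduled, and eligibility includes a clinical judgement. If knowledge of the next arm reached anyone with influence over these steps, patients could be steered, delayed or discouraged. The covariate adjustment in the statistical plan (baseline values, prognostic indicators) can reduce imbalance in what was measured. It cannot do so for unmeasured traits such as motivation.

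**Working it through.** **Who can know the next allocation.** The article gives no figure for this, so the roles are set side by side.

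- Preparing investigator: holds the list; no part in data collection or treatment.
- Study coordinator at each site: receives the completed list; other duties not stated.
- Enrolling investigator at each site: judges eligibility; blinded by the envelopes.
- Treating specialist: opens the envelope after baseline, so sees the allocation of each patient they treat; no stated part in enrolment.
- Outcome assessors: separate staff, blinded.

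The envelopes therefore cover the enrolling investigator. They do not cover the coordinator, to whom all allocations on the list (100%) are available. Whether that matters depends on whether the coordinator also prescreens, consents or schedules, and the article is silent both ways.

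**What the fixed block of 10 adds.** Inputs from Procedures: block size 10, split 5:5, within site; 50 patients per site, so 50/10 = 5 blocks per site and 15 blocks in all. Assume an observer who knows the block size and every past allocation at the site.

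*Certain allocations.* There are C(10,5) = 252 equally likely blocks. An allocation is certain once one arm is used up, which means that all remaining places go to the same arm.

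| Place in block | Blocks in which it is certain | Share |
|---|---|---|
| 10th | 252 | 100% |
| 9th | 2 × C(8,3) = 112 | 44% |
| 8th | 2 × C(7,2) = 42 | 17% |
| 7th | 2 × C(6,1) = 12 | 4.8% |
| 6th | 2 | 0.8% |

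The sum is 420/252 = 1.67 per block, which agrees with 2m/(m+1) = 10/6 for m = 5. That is 16.7% of allocations: 5 × 1.67 = 8.3 of 50 per site, or 15 × 1.67 = 25 of 150.

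*Best guessing.* Always guessing the arm with more places left gives m + 2^(2m−1)/C(2m,m) − 1/2 = 5 + 512/252 − 0.5 = 6.53 correct per 10, or 65.3%, against 50% by chance. Full enumeration of the 252 blocks gives the same two results.

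*Comparison with other block sizes.* Smaller fixed blocks are easier to guess: 70.8% for blocks of 4 and 68.3% for blocks of 6. With randomly varying, undisclosed sizes (simulated, 50 patients per site), an observer who guesses the under-represented arm is right 66.0% of the time for sizes 6/8/10 and 67.8% for 4/6/8. Varying the size removes certainty for someone who does not know where blocks end. It does not lower average predictability.

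**The case against.** The strongest reply is that the article separates the roles well enough. The enrolling investigator is one role, blinded by envelopes. The coordinator is another, with no stated part in enrolment. Envelopes are opened only after baseline data are collected, and assessors are separate and blinded. Coordinator duties and envelope handling are details that a journal article may leave to the full protocol.

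Much of this stands. A reader might infer that the coordinator recruits patients and that concealment has therefore been broken. The article does not say so. Nor does it say that the preparing investigator works at a different location, or that any blinded assessor sees the list. The possibility that patients who know their arm bias self-reported outcomes is a separate measurement problem, and concealment does not solve it.

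What does not stand is the idea that this is only a missing detail. Handing the completed plan to each site is a stated step, and it creates an avoidable route to foreknowledge whoever the coordinator turns out to be.

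A reader might also take the block size of 10, published while Table 1 lists the trial as recruiting, as a serious defect in itself. That is too strong. Ten is a fairly large block, and the 65% and 17% figures need one person who both sees every past allocation and influences entry. The article describes no such person. The treating specialist comes nearest, but enters after baseline, and nothing says that there is only one per site.

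**Conclusion.** The point holds as a risk to concealment. Under the stated procedure a site-based role can know 100% of the allocations on the list before each patient enters, and the envelopes cannot prevent this. No breach is shown. The risk becomes actual only if the list-holder takes part in, or passes information to, screening, consent, eligibility or scheduling. The article does not settle that.

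The block size is secondary. About 1.67 of 10 allocations are certain and about 65% guessable, but only to an observer with full knowledge of past allocations who also controls entry. Sample size and power are unaffected. The change is worth making because it is cheap and because selection on unmeasured traits cannot be repaired in the analysis.

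**What to change.** For the remaining allocations:

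1. Keep the schedule with the preparing investigator only.
2. Have that person supply sequentially numbered, sealed opaque envelopes to each site, or release assignments one at a time. They would be opened after baseline, as already planned.
3. Withdraw the lists now held at the sites.
4. Bar anyone who has held a list from screening, consent, eligibility decisions and outcome assessment. If coordinators are already barred, say so in the protocol.

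The cost is a small one-time set-up task, plus some reassignment of duties if a coordinator does recruit at present.

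Optional: redraw the unused blocks with varying, undisclosed sizes. This removes the certain end-of-block allocations for anyone who does not know the boundaries. Average guessing would be about 66% for 6/8/10 or about 68% for 4/6/8, against 65% now, so the larger set gives up less.
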